### Interim analyses {21b}

Given that the designed interventions are non-invasive, cost-free, and not considered to be expensive, interim analyses are not deemed necessary. Additionally, the sample size has been predetermined in advance.

### Methods for any additional analyses {20b}

Our study does not plan to conduct any additional analyses beyond the intended outcomes. The statistical methods used to analyze the outcomes are clearly mentioned in the text. If any additional or subgroup analysis of variables or confounding factors becomes necessary during the study, it will be justified in the final paper and reported in a section titled “Secondary data analysis.”

### Methods in analysis to handle protocol non-adherence and any statistical methods to handle missing data {20c}

In order to increase adherence, patients will be contacted weekly and given gifts like toys, edibles, and accessories for more encouragement and cooperation. Treatment will be done in a well-designed room and accompanied by music. Missing data will be disposed of with the Multiple Imputation (MI) method.

### Plans to give access to the full protocol, participant-level data, and statistical code {31c}

To obtain access to the complete protocol, participant-level dataset, and STATA statistical codes for public use, interested parties must send a formal reasonable email request to the study’s corresponding author (MK). This is a necessary requirement for eligibility.

## Oversight and monitoring

### Composition of the coordinating center and trial steering committee {5d}

The coordinating center in this study is the specialized lung department in the Children’s Medical Center Hospital and its secretary contacts CF patients daily and arranges appointments. The project management group of the trial consists of the conductor (NH), the corresponding author (MK), and other authors of this study (SS, [name], AE, [name]). The team will be in daily contact through social media and will monitor study conduct and data collection. The trial steering committee includes members of the physical therapy department of the Iran University of Medical Sciences and two lung specialists at the hospital. The meetings of this committee will be held once or twice a month and the conduct of the study and data collection process will be reported and analyzed in the form of slide presentation.

Stakeholders of this trial are CF patients, their families, and health care providers and their comments and suggestions will be gathered in a feasibility study, and if they are helpful with the improvement of the design, they will be implemented; accordingly, if any modifications to the study seem necessary, they will be reported and justified as amendments on IRCT.ir and in the final paper.

### Composition of the data monitoring committee, its role and reporting structure {21a}

The data monitoring committee consists of two of the authors (MK and [name]), a lung specialist doctor ([name]), and the statistician who will double check and analyze data and documents systematically, every week after it is entered into the STATA software by the conductor (NH).

### Adverse event reporting and harms {22}

At the end of the study, a questionnaire will be completed by patients or their parents to evaluate any unwanted side effects that may have occurred during the study and are reported in the order of prevalence. The adverse events most frequently reported are summarized in Table 4 and the adverse events questionnaire is provided in Supplemental file 4.

**Table 4 Tab4:** Adverse events

Adverse events	Number	Percentage per total treatment
Shortness of breath and difficulty breathing		
Aggravation of coughs		
Pain in chest and rib cage		
Weakness and tiredness		
Gastroesophageal reflux		
Muscle soreness in lower limbs		
Nausea		
Dizziness		

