### Interventions {11a}

The treatment session will commence 30 min after the first examination. Group A will first include the main treatment of CPT and then a placebo of aerobic exercise; group B will first include the main treatment of aerobic exercise and then a placebo of CPT (the inverse of Group A). The study will be conducted over 6 weeks, 3 times a week, with a total of 18 sessions. Make-up sessions will be allowed if a session is missed. The duration of the entire treatment session will last approximately 70 min.

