### Group A (CPT and sham aerobic exercise)

At first, the participants will be placed in six standard postural drainage positions for a total of 30 min (Additional file 1: Supplemental Fig. 1A to F). Manual percussion and vibration will be performed on draining segments, in each position for 3–5 min. After completing the previous steps, the patient will be asked to sit down and cough for 1–2 min to expel the extracted secretions. In the following, in order to keep the patients blinded, the placebo aerobic exercise will be applied using a motorized stationary bike in two 15-min sections (Additional file 1: Supplemental Fig. 2). Between the two parts, 1–2 min will be allocated for rest. Throughout the exercise, the heart rate and percentage of arterial oxygen saturation (SpO2) of the patients will be monitored by a pulse oximeter. In this group, in order to eliminate the aerobic effects of the exercises, based on the method of previous studies [37], increasing the respiratory demands and breathing ventilation will be avoided until the end of the study. Therefore, the heart rate of the subject will not exceed 40% of HRmax during 30 min [38]. The total time of the exercises is 30 min, and at the end, 1–2 min will be given for coughing, if needed.

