### Group B (aerobic exercise and sham CPT)

Progressive aerobic exercises will be conducted in two parts; the first will be 15 min on the treadmill and then a further 15 min on a stationary bike. Between the two sets, rest will be given for 1–2 min. A warm-up of 3 min with a gradual increase in speed will take place, and then 24 min of aerobic exercise with determined intensity (12 min on the treadmill and 12 min on a stationary bike), and finally a 3-min cool-down with a gradual decrease in speed will be conducted (Additional file 1: Supplemental Fig. 3A and B).

Throughout the training, the heart rate and SpO2 of patients will be monitored by a pulse oximeter. If there is a sharp drop in SpO2 below 85%, the heart rate is disproportionate to the conditions, and symptoms of severe shortness of breath or any other warning signs appear, the exercise will be stopped. During 24 min of aerobic exercises, the intensity of the exercise will be controlled through the heart rate of the patients (Table 2).

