#### Secondary outcomes

Pulmonary function (FVC): FVC will be measured through a spirometry test, the same as FEV1.

Quality of life (CFQ-R): Quality of life will be subjectively assessed by the Persian version of the Cystic Fibrosis Questionnaire-revised (CFQ-R) [43, 44]. This questionnaire examines different domains (physical functioning, vitality, emotional state, social functioning, role functioning of the individual, body image, eating disorders, treatment burden, general perception of health, respiratory, and digestive symptoms) affecting the quality of life of the person in the last 2 weeks and has been prepared in 3 versions according to the age of the patient. The differing versions are for:Children 6 to 13 years oldParents of above-aged childrenAdults 14 years old and older

The scale of answering questions is a 4-point scale. Total points are calculated and standardized in the range of 0 to 100. The closer the final score is to 100, the higher the quality of life. The MCID for the physical domain is 11.4 points increase, and for the respiratory domain, 7.3 has been calculated [36]. The validity and reliability of the Persian-translated version of the CFQ-R have been evaluated by Talebi et al. [43, 44]. The Cronbach-alpha for the CFQ-R was 0.65–0.91 for the children and parents versions, and ≥ 0.70 for the adult version, showing good internal consistency.

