### Sample size {14}

The prevalence of CF disease is lower in the Asian continent [1] as reported as 1 per 100,000–350,000 in the Middle East and 1 per 100,000 in Iran [5]. Thus, the number of diagnosed CF patients is low. On the other hand, the coordinating center has dedicated the CF specialized clinic of the Children’s Medical Center Hospital to the trial team, for a limited short time frame. Considering these factors, we selected the randomized controlled trial study by Sosa et al. [45] which was closest to our trial in terms of methodology and variables, as the basis for sample size calculation. In this study, 22 participants, 11 in each group, were recruited. Adding a 30% drop-out rate probability to each group, we anticipate recruiting 15 participants in each trial arm. Using power analysis, the required sample size with a power of 0.8 and an α of 0.05, a total sample size of 30 children and adolescents is determined.

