### Plans to promote participant retention and complete follow-up {18b}

Participant retention and complete follow-up are promoted by the monitoring of the physical therapist. In case of withdrawal of patients from the study, their data will be counted as drop-outs.

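### The only stated source for harms is an end-of-study questionnaire for patients or parents, which is poorly suited to SpO2 drops and stopped sessions that the therapist observes

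*Protocol article*

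**What the plan says.** Adverse event reporting and harms {22} fixes the method. When the study ends, "a questionnaire will be completed by patients or their parents to evaluate any unwanted side effects that may have occurred during the study". It adds that "The adverse events most frequently reported are summarized in Table 4", and it refers to a questionnaire in Supplemental file 4, which is not shown. Table 4 is an unfilled shell with eight symptom rows.

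Sessions are monitored. For the sham exercise in group A, "Throughout the exercise, the heart rate and percentage of arterial oxygen saturation (SpO2) of the patients will be monitored by a pulse oximeter". Group B has the same monitoring, plus a stop rule that opens "If there is a sharp drop in SpO2 below 85" (per cent) and goes on to disproportionate heart rate, severe breathlessness and other warning signs. Implementation {16c} has a physical therapist deliver the treatment.

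On duration, Interventions {11a} states: "The study will be conducted over 6 weeks, 3 times a week, with a total of 18 sessions". On withdrawal, Plans to promote participant retention {18b} states: "In case of withdrawal of patients from the study, their data will be counted as drop-outs".

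**The concern.** The plan treats a marked fall in SpO2 as serious enough to stop exercise, yet the only route it states from such an event to the harms report is the memory of a child (from age 6) or a parent at the end of the study. Either may remember that a session was cut short. Neither is likely to know the reading or the therapist's reason.

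Trial design {8} says that a significant advantage would lead to aerobic exercise being recommended among treatment priorities. The harms account published beside that recommendation could, if the text is followed as written, lack falls in SpO2 during exercise and the number of stopped sessions with their reasons. It could also lack events in children who left before the form was given out.

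**Working it through.** The plan gives no harms figure to reproduce. The check sets the sections side by side and asks whether any of them supplies a second source.

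**1. What the form must cover.** From Interventions {11a} and Sample size {14}:
- Sessions per child: 6 weeks × 3 = 18.
- Sessions per arm: 15 × 18 = 270.
- Sessions in all: 30 × 18 = 540.

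Each child contributes one form at the end for up to 18 sessions.

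**2. Who is placed to know each kind of event.**

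| Event | Seen by | Can the form capture it? |
|---|---|---|
| Breathlessness, cough, dizziness, tiredness, pain | Child, perhaps parent | Yes, subject to recall |
| Session part stopped early | Child and therapist | The stop perhaps; the reason probably not |
| SpO2 below 85% | Therapist, by oximeter | Unlikely |

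**3. Whether another section fills the gap.**
- Strategies to improve adherence {11c}: regular contact lets patients mention symptoms promptly. This is offered as an aid to motivation, with no stated link to the harms report and no bearing on oximeter readings.
- The missing-data and non-adherence section {20c}: weekly contact, for adherence.
- Data management {19}: mentions process details, forms and logbooks, in the context of storage and confidentiality.
- The data monitoring committee section {21a} and the auditing section {23}: weekly checks of data and documents, with no mention of adverse events.
- Retention {18b}: withdrawn children are counted as drop-outs, with nothing on whether they complete the form.

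None of these states a second harms source.

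**4. The percentage column in Table 4.** It is expressed relative to total treatment, without further definition. If that means per session (an assumption), end-of-study recall would have to yield a session count, which it does poorly.

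**5. What a harms report of this size can show.** With no affected child, the two-sided 95% Clopper-Pearson upper limit is 1 − 0.025^(1/n):
- n = 15: 21.8%.
- n = 11 (the per-arm number before the drop-out allowance): 28.5%.

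Any harms report from this trial is therefore descriptive, however the data are collected.

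**6. Cost of a session record**, at an assumed one minute each: 540 min = 9.0 h. If each arm had only 11 children, 2 × 11 × 18 = 396 min = 6.6 h.

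**The case against.** The strongest reply is that this argues from silence. The harms section does not say that the questionnaire is the sole source. A journal article leaves session forms to the full protocol, and the questionnaire itself is not shown. The form asks about any unwanted effect, and several triggers or companions of a stop, such as breathlessness and dizziness, are symptoms that a family can report. SpO2 is used to run the session and is never named as a harms outcome.

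Much of this stands. It narrows the point to oximeter readings, reasons for stopping, and children who leave. It does not remove the point, because the article does state who supplies the harms data, with what instrument and when. That is a chosen method, and a better one is within easy reach.

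A reader might infer more than the documents support:
- **That the readings go unrecorded.** The text does not say so, and a session log may exist.
- **That Table 4 is a closed list, or pools the arms.** It is an empty shell for the most frequent events and shows neither.
- **That the recall period breaks the plan's own standard.** The CFQ-R covers factors "affecting the quality of life of the person in the last 2 weeks", but that is the window of a quality-of-life instrument. It sets no standard for recalling adverse events.
- **That about a quarter of harms forms will be lost.** The plan says "Adding a 30% drop-out rate probability to each group, we anticipate recruiting 15 participants in each trial arm". Going from 15 to 11 is a recruitment allowance, and the text does not say that withdrawn children skip the form.

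It is also fair to object that capturing only SpO2 and exercise stops would load the harms table against exercise and leave CPT events to recall. The fix has to cover both parts of the session in both arms.

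**Conclusion.** The point holds in limited form. The one stated harms source is an end-of-study questionnaire for patients or parents. It is a weak instrument for SpO2 below 85% and for early stops with their reasons, and its completion by withdrawn children is not stated.

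The size cannot be put as a number of missed events. The documents give no event rate, and it may be low, since the eligibility criteria exclude severe hypoxia, FEV1 below 30% and need for oxygen with exercise. The conclusion does not depend on any rate. It rests on the harms section being followed as written and on no unseen document linking a session record to the harms report.

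This is a cheap improvement at low-to-moderate priority. It touches safety reporting only.

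**What to change.** Amend Adverse event reporting and harms {22} so that, besides the questionnaire, the therapist records the following at every session in both arms, on the checklist already used each session under Strategies to improve adherence {11c}:
1. any adverse symptom during either part of the session (CPT or sham CPT, exercise or sham exercise) or since the last session;
2. any early stop of either part, with the reason;
3. any SpO2 below 85% during the exercise or sham-exercise part.

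Report these descriptively by randomised arm for all children with at least one session, including those later withdrawn, as children with an event (n/N) and events per session delivered. State that SpO2 monitoring is described only for the exercise or sham-exercise part and that the written stop rule applies to group B, so items 2 and 3 are not a like-for-like comparison between arms. Because the statistician is to stay blind to allocation, withhold free-text reasons until the outcome analysis is done.

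If a session log already holds these items, a sentence saying that it feeds the harms report would be enough. No clinical threshold or stop rule changes.

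The cost is about one minute per session, roughly 9 therapist hours. The oximeter, the therapist and weekly data entry are already in place. There are three downsides. The recorder is unblinded, so noting may be selective. The amendment needs ethics committee approval (Protocol amendments {25}). Sessions already delivered are not covered, and Trial status shows that enrolment had begun.

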### Eligibility criteria {10}

Table 1 summarizes the inclusion and exclusion criteria for the groups. Participants must meet all the eligibility criteria to be included.

**Table 1 Tab1:** Inclusion and Exclusion criteria of the study

Inclusion criteria	Exclusion criteria
1- Confirmed diagnosis of cystic fibrosis based on positive sweat test or genetics test by a specialist doctor	1- Active hemoptysis, pneumothorax, hemodynamic instability, severe hypoxia, acute airway infection, and cognitive disorders
2- Age 6 to 18 years	2- Having cardiac disease such as heart failure or arrhythmia, neurologic and orthopedic disorders, or chest trauma
	3- History of fever, IV antibiotics, or hospitalization in the last 1 month
	4- Having severe uncontrolled gastroesophageal reflux
	5- Severe lung disease (FEV1% < 30%)
	6- Lung transplantation or on the waiting list
	7- Requirement of additional oxygen with exercise
	8- Having uncontrolled diabetics
	9- Improper patient cooperation during treatment sessions
	10- Absence in 3 or more consecutive sessions

The age range considered for inclusion criteria is 6–18. Based on the review and study of patient archives and registrations in the center, most of the patients who are referred to the CF specialized clinic are between the ages of 6 and 18, and this age range is the most accessible. In addition, those who are outpatients mostly have the same stage of chest disease; otherwise, patients with higher and more acute stages of chest disease are hospitalized and those with better conditions and in milder stages usually do not have routine clinical visits and are referred only for check-ups. Thus, participants will be among patients with more similar conditions.

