### Strategies to improve adherence to interventions {11c}

To improve patient motivation, the comprehensive rehabilitation protocol will be offered completely free of charge, ensuring a seamless connection between the patients and their dedicated team of healthcare professionals including the physiotherapist (NH) and physicians. This regular contact will enable patients to promptly communicate any symptoms they may experience. Participants will be given gifts like toys, edibles, and accessories for more encouragement and cooperation. These gifts will be of equal value and given to the patients at the end of the treatment session, in packages. Also, the treatment room has been well designed in colors and music will be accompanied, to provide a better environment for children. In addition, patient adherence to home ACT, ACBT, will be checked at the beginning of every session and marked in a provided checklist. Participants will be called adherent if at least 90% of the prescribed ACT is successfully performed.

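### The harms summary table is selected by frequency and holds eight symptom complaints, so a rare serious event has no row in it, and the text names no separate reporting of serious events.

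*Protocol article*

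**What the plan says.** Under Adverse event reporting and harms {22}, patients or parents complete a questionnaire at the end of the study "to evaluate any unwanted side effects that may have occurred during the study and are reported in the order of prevalence". The section continues: "The adverse events most frequently reported are summarized in Table 4", and "the adverse events questionnaire is provided in Supplemental file 4".

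Table 4 is an empty shell with eight rows: breathlessness, worse cough, chest or rib pain, tiredness, reflux, leg muscle soreness, nausea and dizziness. It has one column for a number and one for a percentage relative to total treatment, a term that is not defined. It has no columns for the two arms.

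Elsewhere the article names graver conditions. The exclusion criteria in Table 1, under Eligibility criteria {10}, include "Active hemoptysis, pneumothorax, hemodynamic instability, severe hypoxia, acute airway infection, and cognitive disorders" and "History of fever, IV antibiotics, or hospitalization in the last 1 month". In the aerobic exercise arm, one of the signs for stopping exercise begins "If there is a sharp drop in SpO2 below 85" per cent. Under Strategies to improve adherence {11c}, the article adds: "This regular contact will enable patients to promptly communicate any symptoms they may experience".

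**The concern.** Frequency is a reasonable way to order common complaints and a poor way to decide which harms a summary shows. In a trial of 30 children a serious event will be rare if it occurs at all, so a rule that favours frequent events works against the ones that matter most. Here the rows are also named in advance, and every one is a symptom.

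The abstract, Trial design {8} and the Discussion all say that a clinical priority between the two treatments may be drawn from this comparison. A summary that shows leg soreness and has no line for a hospital admission in one arm could be read as saying that no serious event occurred. With arms of 15, a stated zero or a stated single case is nearly all that this trial can offer on serious harm.

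**Working it through.** This is mainly a comparison of texts. The plan gives no harms rate or harms calculation to reproduce.

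**Step 1. Events named elsewhere against Table 4.**

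| Event | Where the article names it | Row in Table 4 |
|---|---|---|
| Haemoptysis | Table 1, exclusion 1 | none |
| Pneumothorax | Table 1, exclusion 1 | none |
| Severe hypoxia or desaturation | Table 1, exclusion 1; stopping signs, Group B | none |
| Acute airway infection | Table 1, exclusion 1 | none |
| IV antibiotics | Table 1, exclusion 3 | none |
| Hospitalisation | Table 1, exclusion 3 | none |
| Severe breathlessness | stopping signs, Group B | yes (breathlessness, ungraded) |

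None of the eight rows covers the first six events, and there is no row for serious or for other events. The sentence on Table 4 does not say whether its frequencies are those seen in this trial or those known beforehand. On either reading a rare serious event has no row.

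**Step 2. How one serious event would look.** Inputs: 30 children, 15 per arm (Sample size {14}); 18 sessions each (Interventions {11a}).

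- Per child in one arm: 1/15 = 6.7%
- Per child overall: 1/30 = 3.3%
- Per session, if total treatment means sessions (an assumption): 30 × 18 = 540, and 1/540 = 0.19%

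On each denominator a single event stands at or near the bottom of a list ordered by prevalence. It may tie with symptoms that are also reported once.

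**Step 3. Is such an event plausible?** The documents give no rate, so the six-week risk p per child is an assumption. The chance of at least one event among n children is 1 − (1 − p)^n.

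| Assumed p | Expected events in 30 | At least one in 30 | At least one in 15 |
|---|---|---|---|
| 2% | 0.6 | 45% | 26% |
| 5% | 1.5 | 79% | 54% |
| 10% | 3.0 | 96% | 79% |

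**Step 4. What a zero would mean.** With 0 events in 15, the upper limit for the risk is 1 − 0.05^(1/15) = 18.1% (one-sided 95%) or 1 − 0.025^(1/15) = 21.8% (two-sided 95%). These limits come from the arm size, not from the layout of Table 4. They show why a zero has to be stated with its denominator and not inferred from a missing row.

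**The case against.** The best defence is that the section sets an order and not a cut-off. The questionnaire is open to any unwanted effect, and an event that ranks last is still reported. Only the sentence on Table 4 selects by frequency, and it concerns a summary. Supplemental file 4 may hold an open item or a serious-event item. The source is also a journal article, and definitions of serious events and their reporting routes are commonly left to the full protocol.

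Most of this stands, and it rules out several stronger readings:

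- A reader might infer that serious events have no place in the harms result at all. The documents do not say so: Table 4 is not described as the whole result, and the questionnaire cannot be checked here.
- A reader might take Table 1 as the investigators' list of dangers of these two treatments. Table 1 gives entry exclusions without reasons, and they can equally be read as requirements for clinical stability.
- A reader might infer that an admitted child would appear only as a drop-out, since exclusion 10 concerns three or more consecutive absences and withdrawals are counted as drop-outs. Make-up sessions are allowed, and the article does not say how an admission is treated. This is possible but not stated.

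What the defence does not answer is the selection rule for the summary. An open questionnaire item helps to collect a serious event but gives it no line in a table chosen by frequency. The contact about symptoms during the trial is described as a means of supporting adherence, not as a route for reporting harms.

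**Conclusion.** The point holds for the summary table and the visible text, and no further. As written, the harms summary is chosen by frequency and limited to eight symptom complaints without a split by arm, and no separate reporting of serious events is named. A rare serious event would have no row there and would rank at or near the bottom of the ordered list, although it may still be collected and reported elsewhere.

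The size depends on an event rate that the documents do not give. Over the assumed range of 2% to 10% per child, the chance that the trial meets at least one such event is 45% to 96%, so the case is not remote. These figures assume that all 30 children are followed and that their risks are independent and equal. The analysis of the efficacy outcomes is not affected. This is a flaw in how harms are presented, worth correcting because the comparison is meant to inform a treatment priority and the correction is cheap.

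**What to change.** Keep the eight symptom rows. Add to the harms result a listing by arm of:

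- all serious events, including haemoptysis, pneumothorax and severe desaturation where they occur and meet the trial's definition of serious;
- acute respiratory infection, IV antibiotic courses and hospitalisation, each as its own line.

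Give each as the number of children with the event, whatever its frequency and including zeros, with the number of children in the arm as denominator. State for Table 4 whether its percentages are of children or of sessions. Check Supplemental file 4 and, if it does not already ask about these events, add the items.

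The cost is a few questionnaire items and table lines, with no added visit or procedure. Admissions or antibiotic courses given elsewhere would rest on patient or parent report and could be incomplete. Recruitment has started, so the change would go through the route under Protocol amendments {25}.
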